### Exploratory measures

4.3

#### Near-infrared spectroscopy (NIRS) imaging

4.3.1

Near-infrared spectroscopy (NIRS) is a technique specifically designed for continuous, real-time monitoring of cortical hemodynamic changes during interventions, making it suitable for therapeutic modalities such as acupuncture or intravenous infusion, which elicit immediate and sustained physiological effects. In contrast, flunarizine hydrochloride is administered orally once daily at bedtime, and its pharmacological effects are cumulative and not temporally aligned with the NIRS measurement period. Consequently, NIRS is unable to effectively capture its underlying mechanisms in real time.

NIRS non-invasively measures real-time changes in cerebral oxygenated hemoglobin (O_2_Hb), deoxygenated hemoglobin (HHb), total hemoglobin (tHb), tissue saturation index (TSI). TSI is defined as (O_2_Hb/tHb) × 100%, quantifying the percentage of tissue oxygenation. It is automatically calculated and displayed in real-time on the PortaLite software interface.

Under normal conditions, increased neuronal metabolic demand elevates regional cerebral blood flow disproportionately to oxygen consumption, resulting in a characteristic NIRS pattern of increased O_2_Hb and decreased HHb concentrations (26). The prefrontal cortex (PFC, excluding primary and secondary motor cortices) plays a key role in pain response and subjective perception modulation, serving as a regulatory region for opioid and other analgesic mechanisms (27). Previous studies (28, 29) demonstrated that during head-down positioning or task execution, migraine patients exhibited significantly smaller increases in tHb and mean O_2_Hb concentrations compared to healthy controls, suggesting potential PFC impairment or diminished vasodilatory responses (29).

This study employ a portable NIRS device (PortaLite MKII) for continuous real-time monitoring of the affected PFC on days 1, 8, 15, and 22 of treatment. Parameters include O_2_Hb, HHb, tHb, and TSI.

##### Procedure

4.3.1.1

Preparation: participants are acclimated for 10 min in a quiet, dimly lit room to stabilize physiological baselines. Caffeine and alcohol intake are prohibited for 24 h prior to measurement, and strenuous exercise is forbidden to minimize systemic hemodynamic fluctuations. The PortaLite NIRS device is calibrated according to the manufacturer’s instructions prior to each use.Test: participants sit upright with the PortaLite secured over the affected PFC, positioned according to the Fp1/Fp2 landmarks of the international 10–20 EEG system (30). Sampling frequency is set at 50 Hz, and optodes are shielded with black cloth to minimize ambient light interference. A head fixation strap is used to control motion artifacts during recording. Drift and noise are eliminated during post-processing using filtering techniques. After a 5-min eyes-closed resting adaptation period to stabilize physiological baselines, a 5-min resting-state recording is obtained. Following FSN needle insertion into the upper trapezius (three needle sets with retention), a 5-min post-treatment resting-state recording is acquired. Additional FSN is administered to other target muscles post-measurement.

### Follow-up and recurrence assessment

4.4

Outcome measures are assessed at baseline (Day 0), at the end of treatment (Day 28), and during the post-treatment follow-up period (Days 28, 56, 84, 112, 140, and 168) to monitor the long-term durability of efficacy and the recurrence of symptoms.

Recurrence is defined as a return of monthly migraine days (MMD) to ≥80% of the baseline level during the follow-up period, as recorded in headache diaries. In the event of recurrence, management included referral for clinical follow-up (e.g., re-evaluation in a neurology outpatient clinic) and documentation of acute medication use (e.g., ibuprofen), without re-intervention to assess the natural persistence of treatment effects. Recurrence events are analyzed as a secondary endpoint.

## Safety assessment

5

The primary clinical adverse reactions associated with Fu’s acupuncture needling are subcutaneous hemorrhage and needling syncope. Before the procedure, the operator should avoid needling in areas with dense vascularization. Upon completion of each Fu’s acupuncture session, prolonged pressure should be applied to the needle insertion site and along the needle track to prevent subcutaneous hematoma. Subcutaneous hematomas are graded according to the CTCAE criteria as follows: Grade 1 (Mild): Small hematoma with a diameter <2 cm; managed with local compression or observation. Grade 2 (Moderate): Hematoma measuring 2–5 cm; managed with compression, heat therapy, and temporary discontinuation of treatment if necessary. Grade 3 (Severe): Hematoma >5 cm with persistent bleeding; treatment is discontinued, and the patient is referred for clinical management.

In cases of needling syncope, the needles should be immediately removed. The participant should be placed in a supine position with legs elevated, and vital signs should be monitored. Symptomatic management, such as oxygen administration and hydration, should be provided as needed. Severe cases require prompt medical attention.

Flunarizine’s frequent adverse events are sedation, weight gain and extrapyramidal reactions (31). Body weight is measured every 2 weeks (on days 1, 14, and 28) to quantify weight increase (a change of ≥5% from baseline is considered clinically significant). Extrapyramidal symptoms (EPS), including tremor, akathisia, dystonia, and rigidity, are assessed using the Rating Scale for Extrapyramidal Side Effects (RSESE). Evaluations are conducted at baseline, Week 2, Week 4, and during follow-up by trained neurologists.

Criteria for drug discontinuation included persistent sedation (lasting ≥3 days and interfering with daily activities), moderate to severe EPS (CTCAE grade ≥2), or weight gain of ≥7% accompanied by the patient’s request to withdraw. All events are recorded in patient diaries and reviewed weekly by assessors.

All serious adverse events (SAEs) must be reported to the Ethics Committee within 24 h.

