### Randomization and blinding

2.5

All eligible participants who provide informed consent are randomized in a 1:1 ratio to either the FSN group (*n* = 22) or the drug group (*n* = 22). Randomization is performed using a random number table with allocation concealment. The randomization sequence (seed 12345) is generated by methodology personnel not involved in treatment or evaluation using SAS 9.4 software, with a total of 44 random numbers selected. Forty-four allocation cards are prepared, each labeled with a sequential number and a corresponding random number. The cards are sealed in opaque envelopes marked with matching sequential numbers. The envelopes are kept by the statistician. Upon enrollment, the methodologist open the envelope corresponding to the participant’s sequential number and assign the participant to a group based on the random number.

Participant recruitment, intervention administration, outcome assessment, and statistical analysis are conducted independently by different researchers. Due to the nature of acupuncture, neither participants nor practitioners are blinded, but they are instructed not to disclose group allocation during follow-up assessments. To minimize measurement and subjective biases, a unified operational manual is developed to standardize all outcome assessment procedures. Outcome assessors and data collectors are blinded to group allocation and underwent a two-day training program, during which they are instructed not to communicate with participants regarding the intervention. Participants are also directed not to disclose their treatment assignments to the assessors and instructed to record symptoms based on actual experiences, avoiding the influence of treatment expectations. Data analysis is performed by blinded statisticians.

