### Oral flunarizine hydrochloride

3.2

Participants in the drug group are administered 5 mg flunarizine hydrochloride capsules nightly before sleep for 4 weeks and complete a medication monitoring form after each dose. After the 28th doses, participants will submit their medication monitoring forms to the investigators for review. Close follow-up will be conducted by the investigators during the medication period, and treatment will be immediately discontinued upon occurrence of any adverse events. If necessary, symptomatic treatment will be administered until the adverse events resolve.

Management of Missed Doses: a missed dose is defined as failure to administer the 5 mg dose within a 24-h period. Subjects are required to record each administration in their medication diary. If a dose is missed, no additional dose is to be taken to compensate; instead, the regular dosing schedule is to be resumed at the next planned administration time. All instances of missed doses are recorded in the diary and considered in the adherence analysis.

Study personnel review the medication diaries at each follow-up visit. Adherence is calculated as the percentage of actual doses taken relative to the total planned number of doses (28 doses). Subjects with an adherence rate below 80%were flagged for handling in the sensitivity analysis.

In cases of severe pain (VAS score >8), participants are permitted to take acute analgesic medication. In accordance with the Chinese Guidelines for Migraine Diagnosis and Treatment (25), ibuprofen sustained-release capsules are recommended for pain relief (one capsule per dose, no more than twice daily). If ibuprofen is ineffective, participants could take previously effective analgesics, with detailed records in headache diaries, including drug name, administration time, dosage, and time to headache relief after medication. Prophylactic migraine medications are prohibited.

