This study has several limitations. This study is a single-center trial with a small sample size (*n* = 60), which may be subject to selection bias, thereby limiting the generalizability of its findings to different populations or settings. Due to the inherent characteristics of acupuncture and pharmacotherapy, blinding both practitioners and participants presents considerable challenges, potentially increasing the risk of bias. To mitigate this risk, the intervention operators, outcome assessors, data collectors, and statisticians are all independent researchers. All personnel, except the operators, remained blind to group allocation. Standardized operating procedures are implemented to ensure adherence to treatment and assessment protocols, thereby minimizing unintended influences on outcome measures. The use of rescue medications may interfere with the evaluation of headache intensity and frequency; therefore, the final analysis will comprehensively document and compare intergroup medication usage (dosage, frequency, time to onset). Subsequent studies should establish unified guidelines. Limited by current equipment, near-infrared spectroscopy monitoring focused solely on hemodynamic changes in the prefrontal cortex and did not assess the effects of FSN on other brain regions. As an exploratory study, this trial aimed to investigate whether FSN may reduce patients’ reliance on flunarizine, decrease drug-related side effects, and provide a safe alternative for patients with contraindications to medication. Future large-scale, multi-center clinical trials are warranted to validate the long-term efficacy of FSN and its potential as an adjuvant or first-line treatment.

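### Weekly adverse-event review is given to assessors, the word used for staff who must not learn the allocation, so the claimed assessor blinding is at risk

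*Protocol article*

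**What the plan says.** Section 5 (Safety assessment) sets out the safety review in one sentence: "All events are recorded in patient diaries and reviewed weekly by assessors". The same section links events to arms. For needling it states: "The primary clinical adverse reactions associated with Fu’s acupuncture needling are subcutaneous hemorrhage and needling syncope". For flunarizine it lists sedation, weight gain and extrapyramidal reactions, and it gives criteria for stopping the drug. Extrapyramidal symptoms have their own raters: "Evaluations are conducted at baseline, Week 2, Week 4, and during follow-up by trained neurologists".

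Section 2.5 (Randomization and blinding) makes the blinding claim: "Outcome assessors and data collectors are blinded to group allocation and underwent a two-day training program". It then adds: "Participants are also directed not to disclose their treatment assignments to the assessors". It says openly that participants and practitioners are not blinded.

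Section 7 (Discussion, limitations) widens the claim: "All personnel, except the operators, remained blind to group allocation".

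Section 3.2 (Oral flunarizine hydrochloride) describes drug-arm records. After the last dose, "participants will submit their medication monitoring forms to the investigators for review", and study personnel check the medication diaries at follow-up visits. No equivalent record is described for the FSN arm.

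**The concern.** Blinding of assessors is one of the main safeguards that Sections 2.5 and 7 offer against the bias of an open-label comparison. The safety procedure appears to undo it. Someone who reads each participant's event entries every week will, for some participants, read an entry that could hardly come from the other arm. If that person also reviews headache diaries, raises queries, or administers or scores the VAS, MIDAS or MSQOL, those steps are no longer blind for those participants at Day 28 or at the later visits.

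The opposite risk is also real. Assessors who protect the blind by not looking closely at events would weaken safety ascertainment, although Section 7 names comparison of the adverse-event profiles among the study's purposes.

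**Working it through.** The point rests on comparing sections. The plan states no figure that could be reproduced for it.

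**Step 1: who are the assessors in Section 5?** Section 5 does not say outcome assessors. Section 2.5 uses the bare word for the people to whom participants must not reveal their treatment. The natural reading is that they are the same people, but this is an inference.

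**Step 2: does the conflict depend on that reading?**
- If they are the outcome assessors, Section 5 conflicts with Section 2.5: participants must hide their treatment from people who receive their event entries every week.
- If they are other staff who are not operators, Section 7 still declares them blind, and the same entries contradict Section 7.
- If they are the operators, neither conflict arises, but the article does not say so.

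**Step 3: which records reveal the arm?**

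| Record | Where described | What it reveals |
|---|---|---|
| Haematoma at the needle site, needling syncope | Section 5 | In effect discloses FSN |
| Sedation, weight gain, extrapyramidal symptoms | Section 5 | Suggests flunarizine, does not prove it |
| Medication monitoring form and medication diary | Section 3.2 | Described for the drug arm only |

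The last row is a separate problem for Section 7. The investigators and study personnel who handle these records know the allocation, whether or not they are assessors.

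**Step 4: timing.** If weekly review starts one week into treatment, reviews fall at about days 7, 14, 21 and 28. Three precede the Day 28 primary assessment and the fourth coincides with it. All four precede the post-treatment visits in Section 4.4.

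**Step 5: how many participants (illustration only).** The documents give no event rates. Let p be the share of participants who make a telling entry, assumed to be 5% to 30%, equal in both arms and independent between participants.
- Expected number = 44 × p: 44 × 0.05 = 2.2 and 44 × 0.30 = 13.2.
- Chance of at least one = 1 − (1 − p)^44: 1 − 0.95^44 = 0.895 at p = 5%, and above 0.999 at p = 30%.
- Counting only the FSN arm, where entries are close to conclusive: 22 × 0.05 = 1.1 and 22 × 0.30 = 6.6 participants. The chance of at least one is 1 − 0.95^22 = 0.68 at p = 5%, and above 0.999 at p = 30%.

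Some unmasking is therefore likely, but for a minority of participants over this range.

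**Step 6: route to the outcomes.** The primary outcome is the change in monthly migraine days (Section 4.1), and the migraine data come from daily diaries (Section 4.2) kept by participants who know their treatment. The scales likewise report participants' own pain, disability and quality of life. An assessor who learns the arm can add bias only through diary review, queries, scoring and scale administration.

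**The case against.** The strongest reply is that this is loose wording. Section 5 never says outcome assessors, and the article mentions others who could do the review: the trained neurologists, the investigators who follow participants during medication, and the operators. Section 2.5 also says that recruitment, treatment, assessment and analysis are done by different researchers. The identity of the reviewers is indeed inferred. Even so, no unblinded safety reviewer is named, and Section 7 leaves room for none except the operators.

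Several stronger conclusions are tempting, but the documents do not support them:
- A reader might infer that the primary endpoint is unblinded by the safety process. Migraine days are self-reported by participants who already know their arm. That larger exposure is built into the design, and Section 7 acknowledges the difficulty of blinding them and the risk of bias.
- A reader might infer that assessor blinding is the only protection claimed. Section 2.5 also lists a standard manual, separate roles, blinded statisticians and instructions to participants on recording.
- A reader might infer that assessors grade haematomas or apply the criteria for stopping the drug. Section 5 gives them diary review only, and extrapyramidal ratings go to neurologists.
- A reader might infer that events and headaches are entered in one diary. Section 5 says patient diaries without saying which, and Section 4.2 does not list adverse events among the headache-diary contents.
- A reader might infer that all 22 drug-arm participants are unmasked to assessors through the medication form. Section 3.2 gives that form to investigators, and the medication diaries to study personnel, not to outcome assessors.

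**Conclusion.** The conflict is real. A procedure stated in Section 5 works against a safeguard stated in Sections 2.5 and 7, and the drug-arm records in Section 3.2 make the blanket statement in Section 7 untenable as written. This concerns what the article says, not detail left to a fuller document.

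Its size is moderate to small. Event entries put the blinding at risk only for participants who make a telling one, about 2 to 13 of 44 if the assumed range of 5% to 30% is right, and flunarizine's events are suggestive rather than conclusive. The effect on the primary result is limited to the assessor-dependent steps. The conclusion that outcome blinding is compromised, as opposed to the Section 7 statement being wrong, rests on reading the Section 5 assessors as those of Section 2.5. It should be corrected because the safeguard is claimed and the correction is cheap. It is not a reason to discount the trial.

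**What to change.** In Section 5, state that the weekly review of event and medication records is done by existing staff with no role in outcome assessment or data collection. Keep those records on forms separate from the headache diary, and withhold them from outcome assessors and data collectors. Add the same restriction to Section 3.2 for the medication forms and diaries. In Section 7, replace the statement that only the operators are unblinded with a list of the roles that know the allocation.

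Leave the extrapyramidal ratings with the trained neurologists, as Section 5 already provides. Sections 3.2 and 5 should also be reconciled on who applies the criteria for stopping the drug. That decision belongs to the trial team, and no rule is proposed here.

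The cost is some role wording and slightly more form handling. Section 2.5 already separates the roles, so no new staff should be needed. The trade-off is that events are then reviewed by people who know the allocation. This should be stated, because the adverse-event profiles are to be compared between arms.

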## Statistical analysis

6

Statistical analyses are conducted using SPSS 25. All tests employ two-sided comparisons, with statistical significance defined as *p* < 0.05.

Normally distributed continuous variables are presented as mean ± standard deviation (SD), whereas non-normally distributed variables are reported as median and inter-quartile range (IQR). Categorical variables appear as frequency and percentage (proportions).

For the MMD, MSQOL, MIDAS and VAS scale scores, between-group differences in changes from baseline to 4 weeks post-treatment are analyzed using either the independent *t*-test or Mann–Whitney U test, as appropriate. Intra-group comparisons between baseline and 4-week post-treatment measurements are conducted using paired *t*-test or Wilcoxon signed-rank test. Given the repeated measurements of MMD and the scale scores, repeated-measures analysis of variance (ANOVA) is additionally employed for supplementary analysis. For near-infrared spectroscopy (NIRS)-derived oxygen saturation levels, analyzed for within-group differences before and after treatment using paired *t*-test.

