**Figure 4 fig4:**
[figure not shown]
Placement of NIRS.

**Table 1 tab1:** Study schedule.

Stage	Baseline	Treatment			Follow-up (after treatment)		
Time point	Day 0	Day 1	→	Day 28	Day 28	→	Day 168
Enrolment							
Eligibility	×						
Informed consent	×						
Allocation	×						
Interventions							
FSN		×					
Flunarizine hydrochloride		×					
Assessment							
MMD	×			×	×	×	×
MSQOL scores	×			×	×	×	×
VAS scores	×			×	×	×	×
MIDAS scores	×			×	×	×	×
Headache diaries	×			×	×	×	×
NIRS		4 measurements					
Adverse events	×	×					

Fu’s Subcutaneous Needling (FSN), developed by [name], is a novel acupuncture technique derived from traditional Chinese medicine and grounded in anatomy, physiology, and myofascial trigger point theory. It involves repetitive sweeping of the subcutaneous loose connective tissue over pathologically tense muscles to reduce peripheral muscle tension (19), combined with resistance exercises to promote tissue reperfusion. This approach rapidly alleviates muscle ischemia and hypoxia (20), reduces mechanical compression on surrounding tissues, and demonstrates notable efficacy in pain management (21, 22).

Currently, there is a paucity of clinical studies on the application of floating acupuncture for MWoA, and objective assessments of its therapeutic effects are lacking. Therefore, we propose a randomized controlled trial to assess the clinical efficacy and underlying mechanisms of FSN in treating MWoA, with the goal of identifying safer and more effective treatment strategies. We hypothesize that floating acupuncture is non-inferior to flunarizine hydrochloride in alleviating pain intensity, reducing attack frequency, and enhancing quality of life in MWoA patients.

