### Sample size calculation

2.4

This study is an exploratory investigation, with the primary outcome measure defined as the reduction in the monthly migraine days (MMD) from baseline after 4 weeks of treatment. As a novel acupuncture technique, Fu’s Subcutaneous Needling (FSN) inevitably lacks high-quality randomized controlled trials (RCTs) to inform sample size estimation. Therefore, reference is made to an internationally rigorous RCT on acupuncture for migraine without aura (23), and the sample size is estimated based on this study, combined with clinical FSN practice and the current study design. The hypothesis posited comparable effect sizes between the two interventions (FSN group and flunarizine hydrochloride group) in this trial and those observed in the prior study’s acupuncture and flunarizine hydrochloride groups. The referenced study reported that after 4 weeks of treatment, the MMD in the acupuncture group decreased by 4.1 ± 3.5 from baseline, while the MMD in the flunarizine hydrochloride group decreased by 1.9 ± 2.3 from baseline. To verify whether the efficacy of FSN is at least not inferior to that of flunarizine hydrochloride, a non-inferiority test is employed. Based on previous research (24), the most commonly selected non-inferiority margin for Monthly Migraine Days (MMD) in migraine studies is 1. The calculation is performed using the Non-Inferiority Tests for the Difference Between Two Means in PASS 15.0 software. With *α* = 0.05 (two-sided), power (1−*β*) = 0.9, and an anticipated 25%dropout rate, a total of 44 participants (22 per group, 1:1 ratio) are required to detect a statistically significant difference in MMD changes between the two groups.

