## Conclusion

8

The hypothesis of this study is that FSN therapy is not inferior to flunarizine hydrochloride in improving headache intensity and attack frequency in patients with migraine without aura, and that its therapeutic effects may be sustained over time. The study aims to test this hypothesis in a controlled clinical trial. The results may demonstrate the clinical utility of FSN therapy for migraine without aura and facilitate its wider implementation.

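### The trial is sized for non-inferiority with a 1-day margin, but the analysis section plans only tests of no difference and never uses the margin

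*Protocol article*

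**What the plan says.** The objective is non-inferiority in three places in the protocol article.

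- Introduction (section 1), final paragraph: "We hypothesize that floating acupuncture is non-inferior to flunarizine hydrochloride in alleviating pain intensity, reducing attack frequency", and also quality of life.
- Section 2.4, Sample size calculation: "To verify whether the efficacy of FSN is at least not inferior to that of flunarizine hydrochloride, a non-inferiority test is employed". The margin follows: "the most commonly selected non-inferiority margin for Monthly Migraine Days (MMD) in migraine studies is 1". The size comes from the PASS non-inferiority procedure for two means.
- Section 8, Conclusion: "The hypothesis of this study is that FSN therapy is not inferior to flunarizine hydrochloride in improving headache intensity and attack frequency".

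Two places describe a test of difference instead.

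- Section 2.4 closes by saying that the 44 participants "are required to detect a statistically significant difference in MMD changes between the two groups".
- Section 6, Statistical analysis: "All tests employ two-sided comparisons, with statistical significance defined as" p < 0.05. The between-group change in MMD, and in the three scale scores, is compared by independent t-test or Mann–Whitney U test. Within-group paired tests and a supplementary repeated-measures ANOVA are added. Section 6 contains no margin, no confidence limit to set against one, and no rule for declaring non-inferiority.

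**The concern.** A test of no difference has its null value at 0. A non-inferiority test with this margin has its null value at -1 day (FSN reduction minus flunarizine reduction). The two can give different answers on the same data, and section 6 names only the first.

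A non-significant result is therefore left without a planned interpretation, and in a trial this small it is a likely result. The temptation would be to report it as showing that FSN is no worse. Two incompatible descriptions of the primary test also leave room to choose between them after the data are seen.

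Two further mismatches follow from the same gap. The Mann–Whitney test gives no interval for the difference in means, which is the scale on which the margin and the sample size are set. The Introduction also claims non-inferiority for pain intensity and quality of life, and the Conclusion claims it for headache intensity, although only MMD has a margin.

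**Working it through.** **Inputs (section 2.4).** MMD reduction is 4.1 (SD 3.5) for acupuncture and 1.9 (SD 2.3) for flunarizine, so the assumed advantage is 4.1 - 1.9 = 2.2 days. Margin 1 day, alpha 0.05 stated as two-sided, power 90%, dropout 25%, 22 per arm. Evaluable per arm: 22 × 0.75 = 16.5, taken as 16. Results are also shown for 22 (no dropout).

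**Method.** SE = √((3.5² + 2.3²)/n) = √(17.54/n), with 2n - 2 degrees of freedom and the noncentral t distribution. SE is 1.047 at n = 16 and 0.893 at n = 22.

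**Step 1: what 44 corresponds to.** The distance from the margin to the assumed truth is 2.2 + 1 = 3.2 days.

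| Test, 90% power | Evaluable per arm | After 25% dropout | Total |
|---|---|---|---|
| Non-inferiority, one-sided 0.05 | 16 | 16/0.75 → 22 | **44** |
| Non-inferiority, one-sided 0.025 (two-sided 95% CI) | 20 | 20/0.75 → 27 | 54 |
| Difference of 2.2 days, two-sided 0.05 (normal approximation) | 39 | 39/0.75 = 52 | 104 |

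The stated 44 is reproduced exactly as a non-inferiority size at one-sided 0.05. It is well short of what a 90%-power difference test would need, so the sizing and section 6 describe different tests.

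**Step 2: the difference test at the plan's own 2.2-day advantage.** The noncentrality is 2.2/1.047 = 2.10 at n = 16 and 2.2/0.893 = 2.46 at n = 22. Power for a two-sided p < 0.05 favouring FSN is 53% and 67%.

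**Step 3: the difference test when FSN is worse by the full margin.** The noncentrality is -1/1.047 = -0.96 at n = 16 and -1/0.893 = -1.12 at n = 22. The probability of p > 0.05 is 84.8% and 80.5%. Under a rule that the lower limit of the two-sided 95% CI must exceed -1 day, the probability of declaring non-inferiority at this true value is 2.5% by construction.

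**Step 4: how far the two rules diverge (simulation, normal data, 16 per arm).**

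| True FSN advantage | p > 0.05 | Lower 95% limit above -1 day |
|---|---|---|
| -1 day | 85% | 2.6% |
| 0 | 95% | 15% |
| 2.2 days | 47% | 84% |

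At 2.2 days, 31% of trials meet the margin and yet have p > 0.05. Section 6 has no way to recognise these as successes. The 95% CI half-width is about 2.042 × 1.047 = 2.1 days, roughly twice the margin, so a non-significant result cannot by itself exclude a deficit of 1 day.

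**Step 5: power of a margin-based rule at the planned size.** The noncentrality is 3.2/1.047 = 3.06 at n = 16. With a two-sided 95% CI, power is 84% (94% at n = 22). With a one-sided 0.05 limit it is 91% at n = 16.

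**The case against.** **The primary question is tested by one route.** A reader might infer that nothing in section 6 bears on non-inferiority. That is too strong. A two-sided p < 0.05 favouring FSN puts the lower 95% limit above 0, and so above -1 day. The gap is every other result, together with the 53–67% power of that one route.

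**Nobody says p > 0.05 means non-inferior.** This is correct. The 85% is the risk if non-significance were read that way. It is not the error rate of a rule the protocol states.

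**Two-sided testing is not the fault.** This also stands. A two-sided 95% CI is a standard basis for a non-inferiority decision. The fault is the null value of 0 and the absence of the margin.

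**The article is condensed, and section 2.4 does name a non-inferiority test.** An unseen analysis plan may contain the CI rule. But section 6 does not leave the primary comparison open: it names the test, for all outcomes, and that test is of no difference. This is a contradiction between stated parts, not a missing detail.

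**The trial is called exploratory.** That tempers the consequences. Section 2.4 nevertheless fixes a margin, alpha and power, and the Conclusion presents the study as a test of the hypothesis.

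**Adherence.** Section 3.2 says: "Subjects with an adherence rate below 80%were flagged for handling in the sensitivity analysis". The rule counts drug doses only, and a reader might infer that low adherers will be removed from the control arm alone. The text says flagged, not excluded, and their handling may properly sit elsewhere. No finding is made on it.

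**Conclusion.** The contradiction is real and should be resolved before analysis. The hypothesis, margin and sample size are for non-inferiority, while the named primary test and the last sentence of section 2.4 are for a difference. The margin is not carried into the analysis, and a non-significant result has no planned reading.

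The size: 53% power at 16 evaluable per arm (67% at 22) for the only section 6 result that would imply non-inferiority. If non-significance were taken as success, a treatment worse by the whole margin would pass about 85% of the time (81% at 22), against 2.5% under a CI rule.

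These figures rest on the protocol's SDs of 3.5 and 2.3, approximately normal changes and, for the power figures, its assumed 2.2-day advantage. They do not show that the trial will be misreported, only that the text as it stands would not prevent it.

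**What to change.** **Section 6.** Make the primary analysis the two-sided 95% CI for the difference in mean MMD reduction, FSN minus flunarizine. Declare non-inferiority if the lower limit is above -1 day. If it is, test superiority from the same interval (lower limit above 0), which costs no additional alpha. Do not use the Mann–Whitney test for the primary decision.

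**Section 2.4.** Replace the closing reference to detecting a significant difference with showing non-inferiority.

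**Sections 1 and 8.** Limit the formal non-inferiority claim to MMD, the only outcome with a margin.

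**Cost.** The change is to wording; the rule needs no new data. It does expose a shortfall: with 44 randomised and about 16 evaluable per arm, power is about 84% under the plan's assumptions, not 90%. Section 2.4 should do one of three things:

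- state 84% power with the two-sided 95% CI;
- state that 44 corresponds to one-sided 0.05 (91% at 16 per arm) and use the matching confidence limit;
- raise the total to 54 to keep both the two-sided 0.05 level and 90% power.
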